## Abstract

**Background:**

Infants born very preterm (< 32 weeks gestational age (GA)) are at risk for developmental language delays. Poor language outcomes in children born preterm have been linked to neurobiological factors, including impaired development of the brain’s structural connectivity (white matter), and environmental factors, including decreased exposure to maternal speech in the neonatal intensive care unit (NICU). Interventions that enhance preterm infants’ exposure to maternal speech show promise as potential strategies for improving short-term health outcomes. Intervention studies have yet to establish whether increased exposure to maternal speech in the NICU offers benefits beyond the newborn period for brain and language outcomes.

**Methods:**

This randomized controlled trial assesses the long-term effects of increased maternal speech exposure on structural connectivity at 12 months of age (age adjusted for prematurity (AA)) and language outcomes between 12 and 18 months of age AA. Study participants (*N* = 42) will include infants born very preterm (24–31 weeks 6/7 days GA). Newborns are randomly assigned to the treatment (*n* = 21) or standard medical care (*n* = 21) group. Treatment consists of increased maternal speech exposure, accomplished by playing audio recordings of each baby’s own mother reading a children’s book via an iPod placed in their crib/incubator. Infants in the control group have the identical iPod setup but are not played recordings. The primary outcome will be measures of expressive and receptive language skills, obtained from a parent questionnaire collected at 12–18 months AA. The secondary outcome will be measures of white matter development, including the mean diffusivity and fractional anisotropy derived from diffusion magnetic resonance imaging scans performed at around 36 weeks postmenstrual age during the infants’ routine brain imaging session before hospital discharge and 12 months AA.

**Discussion:**

The proposed study is expected to establish the potential impact of increased maternal speech exposure on long-term language outcomes and white matter development in infants born very preterm. If successful, the findings of this study may help to guide NICU clinical practice for promoting language and brain development. This clinical trial has the potential to advance theoretical understanding of how early language exposure directly changes brain structure for later language learning.

**Trial registration:**

NIH Clinical Trials (ClinicalTrials.gov) NCT04193579. Retrospectively registered on 10 December 2019.

## Background

Each year, approximately 400,000 infants in the United StatesUSA and 15 million worldwide are born preterm (before 37 weeks of gestation) [1]. Up to 50% of infants born less than 32 weeks of gestation develop disadvantaged outcomes, including language and related learning difficulties [2–7]. Poor language skills can lead to poor social relationships [8], academic and occupational underachievement [9], and high utilization of special education [6]. Although many studies of premature birth describe poor language outcomes [2, 6, 7, 10, 11], relatively few propose interventions beyond medical treatment [12].

Poor language outcomes in preterm children have been attributed in part to the minimal amount of maternal speech that neonates experience while hospitalized in the neonatal intensive care unit (NICU) [12–14]. Under typical developmental circumstances, maternal speech is one of the most salient acoustic stimuli experienced by a fetus [15, 16]. The sound environment of an open-bay NICU has been estimated to contain only 2–5% (~ 50 min/day) of adult speech sounds [17]. Studies in older, typically developing infants have demonstrated that the quantity and quality of language input a child experiences are tightly linked to later language skills [18, 19]. Maternal speech input during the first postnatal year is also shown to assist infants’ abilities to recognize speech sounds [20–22]. One observational study of preterm newborns found that variations in the amount of adult speech a newborn heard on a single day in the NICU at 32 and 36 weeks postmenstrual age (PMA) were positively associated with language skills at 7 and 18 months [17]. Small interventional studies have found that experimentally increasing preterm infants’ exposure to maternal speech can significantly improve short-term health outcomes [14], including improvements in oxygen saturation [23, 24], decreases in apnea and bradycardia events [25, 26], improvements in weight gain [26], feeding tolerance [27, 28], and auditory cortex thickness as measured by cranial ultrasound [29]. It is not known yet, however, whether there are sustained long-term benefits of early maternal speech exposure on language outcomes.

Adverse neurodevelopmental and language outcomes in preterm children have also been attributed in part to the susceptibility of white matter to damage from oxidative stress induced by common complications of preterm birth, such as hypoxia, ischemia, and inflammation [30]. Although advances in medical care have reduced the incidences of severe white matter brain injuries (e.g., periventricular leukomalacia), diffuse white matter abnormalities remain a common sequelae of preterm birth. These more subtle white matter abnormalities are more readily detected using diffusion magnetic resonance imaging (dMRI) than with conventional MRI or ultrasound imaging methods. dMRI is an advanced MRI technique used to assess microstructural properties of white matter pathways (or tracts). Metrics derived from dMRI for assessing white matter microstructure include measures such as mean diffusivity (MD) and fractional anisotropy (FA). Studies of preterm newborns have shown these white matter metrics to differ in comparison with term-born infants [31] and to relate to language outcomes at two years of age [32]. In older term-born children, dMRI measures have been found to vary in relation to how much speech children experience from caregivers [33]. Evidence for whether increased speech exposure in the NICU promotes structural changes in white matter connectivity remains limited.

Our aim is to establish whether a language intervention (treatment) administered in the NICU has the potential to promote healthy language and brain development in very preterm infants. To achieve this goal, we have designed an interventional randomized controlled trial (RCT) that will test the causal effect of increased exposure to maternal speech in the NICU on language outcomes and white matter development in infants born very preterm. Our first aim will assess the long-term effects of increased maternal speech exposure on an infant’s expressive and receptive language abilities measured at 12–18 months of age adjusted for prematurity (AA). We focus on these language abilities because they have been linked to language processing abilities that are known to be strong predictors of later academic outcomes [34–36]. We hypothesize that, compared to controls, infants in the treatment group will demonstrate more advanced language skills at 12–18 months AA. Our second aim will assess the effects of increased maternal speech exposure on an infant’s white matter development at ~ 36 weeks PMA and 12 months AA. Measuring white matter development at these two ages will allow us to assess whether possible immediate effects of increased maternal speech exposure on white matter development are sustained over the first year of life. We hypothesize that, compared to controls, infants in the treatment group will demonstrate changes in dMRI measures reflecting increased white matter development. Specifically, infants in the treatment group will demonstrate lower MD.

## Methods

### Study design

To achieve these aims, we propose an RCT that will involve 42 very preterm infants born and cared for at Stanford’s Lucile Packard Children’s Hospital (LPCH). Enrollment is planned from November 2019 to December 2021. For infants who meet the inclusion criteria of gestational age at birth (GA) of 24-0/7 to 31-6/7 weeks, we will obtain informed consent and questionnaires about the family’s demographics and language from parents, and a speech recording from each mother. Infants will then be randomized to the treatment (T) or control (C) group. Infants randomized to either T or C group will receive standard medical care, with the exception that infants randomized to the T group will also receive the maternal speech intervention achieved by playing recordings of maternal voice via iPods placed in an infant’s incubator or open crib. Infants in the C group will have the same auditory setup to ensure that parents and clinical staff remain blinded to the group status. The duration of the intervention will begin once an infant gets transferred to the intermediate care nursery, indicating medical stability, and end once an infant has received their clinical MRI, which is part of the standard medical care at LPCH and is performed prior to hospital discharge (~ 36–38 weeks PMA). The long-term effects of the intervention will be assessed at 12 months and 18 months AA. At 12 months AA, infant participants will undergo a dMRI scan during natural sleep, and parents will complete the MacArthur-Bates Communicative Development Inventories (CDI): Words and Gestures Questionnaire [37]. At 18 months AA, parents will complete another CDI: Words and Gestures Questionnaire, the primary outcome assessment of language development (see Fig. 1).

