#### Randomization and RCT design elements

Eligible participants will be randomized by the principal investigator ([name]), who will not be blinded, in order to provide close monitoring of the procedures. The principal investigator will allocate participants sequentially as they are enrolled to either the T or the C group using the minimization algorithm by Pocock and Simon [41] implemented in the R statistical software package [42]. Randomization will be stratified for (1) GA (24-0/7 to 27-6/7 weeks or 28-0/7 to 31-6/7 weeks), to control for potential development differences in response to the intervention and as a proxy for neural injury, and (2) socioeconomic status (SES) (above versus below average SES; based on Hollingshead Index (HI) [36, 43]), to control for potential differences in language outcomes affected by socioeconomic factors. Taking into account ethical considerations and parental preferences, twins and multiples will be assigned to the same group [44]. Families and research and clinical staff will be blinded to the group status. In the unlikely event that a family, research staff, or clinical staff suspect that an infant may not tolerate the speech recording, the principal investigator will reveal the group assignment.

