#### Delivery of intervention

The intervention will occur for a minimum of 2 weeks (28 h) and a maximum of 9 weeks (126 h) prior to the date of the clinical brain imaging scan. Neonates randomized to the T group (maternal speech group) will listen, via an iPod placed in cribs and/or incubators, to recordings of their mother’s speech at hourly intervals between 10:00 p.m. and 6:00 a.m. Administration of the intervention during periods when parents are unlikely to visit the hospital is expected to minimize parental knowledge for the group assignment. Recordings will be played automatically using the alarm function to avoid reliance on clinical staff. Research staff will regularly check on the status of the device to ensure proper functioning. Neonates will hear a total of 2.67 h of speech recordings per night (20 min/h × 8 h). Treatment length will be defined as the number of nights from the start of treatment (i.e., beginning of PICN stay) to the end of treatment (i.e., date of MRI scan at 36–38 weeks PMA). Within a given hour, two 10-min segments will be randomly presented to avoid synchronization with biological and sleep rhythms. Sound intensity for speech recordings is balanced between open cribs versus incubators and is below hourly NICU safety levels less than 50 dB [45].

Neonates in the C group will receive standard care. All infants in the NICU receive developmental care support from health care providers and families, and clinical staff tracks which activities are experienced by all infants through nursing documentation. Clinical staff uses a standard care path to guide which types of activities are appropriate for an infant depending on the maturity and health status. Families are generally encouraged to talk, read, and sing to their infants when visiting, if the infant is deemed in the appropriate stage. Auditory setup will be the same for neonates in the C group; however, these neonates will not hear speech recordings. This procedure ensures that parents remain blinded to the group randomization.

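### A silent control device masks by sight only, so it does not secure the stated blinding of clinical staff; parents, who score the primary outcome, are only partly protected

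*Protocol article*

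**What the plan says.** **Who is said to be blinded.** The Study design section says: "Infants in the C group will have the same auditory setup to ensure that parents and clinical staff remain blinded to the group status". Randomization and RCT design elements goes wider: "Families and research and clinical staff will be blinded to the group status". Only the principal investigator is unblinded.

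**What the arms receive.** The abstract says: "Infants in the control group have the identical iPod setup but are not played recordings". Delivery of intervention says the same: "Auditory setup will be the same for neonates in the C group; however, these neonates will not hear speech recordings". Treated infants hear "recordings of their mother’s speech at hourly intervals between 10:00 p.m. and 6:00 a.m", from an iPod in the crib or incubator, and "Within a given hour, two 10-min segments will be randomly presented to avoid synchronization with biological and sleep rhythms". The nightly amount is given as "Neonates will hear a total of 2.67 h of speech recordings per night (20 min/h × 8 h". The intervention lasts 2 weeks (28 h) to 9 weeks (126 h), at an intensity below 50 dB.

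**What protects the masking.** Playback is automatic, so staff need not operate the device. The mother's recording is made before randomization (Speech recording procedures). The night window is justified for parents: "Administration of the intervention during periods when parents are unlikely to visit the hospital is expected to minimize parental knowledge for the group assignment". The same section closes by saying that the common setup guarantees parental blinding, and there it names parents only.

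**Who is present and who scores.** The Harms section has clinical staff monitoring the infants for the whole intervention period. Parents complete the CDI at 18 months adjusted age, which is the primary outcome.

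**The concern.** The arms differ in sound, and sound is the feature the control condition leaves unmatched. The device looks the same in both arms, but only one arm's device is ever heard. The hours chosen to avoid parents' visits place all the playback on the night shift, and the step-down unit was preferred partly because it is quieter (Enrollment procedures). Blinding of clinical staff is nevertheless stated as a fact, with the common setup given as the reason.

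For parents, the article is not consistent with itself. One sentence expects the timing to reduce their knowledge of the arm; a later one in the same section treats their blinding as guaranteed.

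This matters because the primary outcome is a parent checklist. A parent who learns the arm, from staff or during an overnight visit, could score differently because of it. Staff who know the arm could also change how much they encourage families to talk and read. The trial could then be reported as blinded to a degree that its design does not deliver.

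**Working it through.** **1. The plan's own playback figure.** From Delivery of intervention: 20 min/h × 8 h = 160 min = 2.67 h per night. This reproduces the stated figure. Fraction of each hour: 20/60 = 1/3.

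**2. The conflicting figure in the same section.** 28 h over 14 nights = 2.0 h per night; 126 h over 63 nights = 2.0 h per night. Spread over 8 hours, that is 120/8 = 15 min/h, or 1/4. At 2.67 h per night the totals would be 14 × 2.67 = 37.3 h and 63 × 2.67 = 168 h. The passages must be reconciled; both fractions are carried below.

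**3. How likely staff are to notice.** Assumptions not in the documents: 3 momentary bedside checks a night, independent of each other, and a probability *a* that a check made during playback hears it. Over the minimum 14 nights there are 3 × 14 = 42 checks. With playback fraction *f*:

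- P(heard on a given night) = 1 − (1 − *fa*)³
- P(never heard in 42 checks) = (1 − *fa*)⁴²

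| *a* | *f* = 1/3: heard on a given night | *f* = 1/3: never heard | *f* = 1/4: heard on a given night | *f* = 1/4: never heard |
|---|---|---|---|---|
| 1 | 70% | 4.0 × 10⁻⁸ | 58% | 5.7 × 10⁻⁶ |
| 0.25 | 23% | 2.6% | 18% | 6.6% |
| 0.10 | 10% | 24% | 7% | 35% |

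The first row assumes that every check during playback hears it, which the article does not establish. The lower rows show that even with poor audibility, staff remain unaware for the whole minimum course in a minority of cases.

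**4. Each safeguard set against each group.**

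- Identical device: hides the arm from sight for everyone, from hearing for no one.
- Automatic playback: removes the need for staff to operate the device, not their ability to hear it.
- Night timing: helps parents, not night staff.
- Recording before randomization: keeps the recording session from revealing the arm; it does nothing about later playback.

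**5. What leakage to parents could do.** The documents give no rate of leakage and no size of reporting shift, so these are assumptions. Mean bias = (share of treatment parents aware) × (shift in SD). The rejection rate under no true effect is that of a two-sided t-test at 5%, 21 per arm, 40 degrees of freedom, noncentrality = bias × √(21/2).

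- 30% aware, 0.3 SD: bias 0.09 SD, rate 5.9%.
- 50% aware, 0.5 SD: bias 0.25 SD, rate 12.4%.
- Wider range, 25% aware with 0.2 SD to 100% aware with 0.8 SD: bias 0.05 to 0.80 SD, rate 5.3% to 72%.

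The range is wide because its inputs are unknown. It shows what would follow from leakage, not that leakage occurs.

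**The case against.** The strongest reply is that audibility is inferred. Sound is held below 50 dB, and the article gives no level outside a closed incubator, no ambient level and no staffing pattern. That stands: a reader might infer that staff certainly hear the recording and cannot stay blind, and the text does not go that far. It shows only that nothing described secures their blinding.

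Second, staff do not score the primary outcome. For it to be biased directly, parents must learn the arm, remember it for over a year and score differently as a result. That also stands. A reader might infer that the primary result is biased by a known amount; the documents support no such figure, and the milder scenario barely moves the error rate. The diffusion MRI outcome is less exposed.

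Third, changed behaviour by staff is partly covered. Activities follow a standard care path and are documented by nursing. Balance is to be tested on language exposure during treatment and after discharge, and home recordings of adult word counts can become a covariate. This reduces the concern about background speech, but it does not address how an aware parent completes a checklist. Masked data handling does not help either when the rater is the parent.

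Fourth, staff instructions and a masking questionnaire may sit in the full protocol, which is not shown. Their absence from the article is therefore not held against it. The point rests on what the article affirms: that staff are blinded, by means that do not achieve it, and that parental blinding is both merely made likelier and guaranteed.

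**Conclusion.** The concern holds in a limited form. The stated blinding of clinical staff is not secured by a silent device of the same appearance. That rests on quoted text: no sound in one arm, 15 to 20 minutes of audible speech per night hour in the other, for 2 to 9 weeks, with staff in attendance. How many staff would notice depends on audibility, which is not given.

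For parents, masking is partial and leakage is a risk of unknown size. The 6% to 12% false-positive rates are illustrations from assumed inputs. Because the primary outcome is parent-reported, the wording should be corrected and the extent of masking measured.

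**What to change.** 1. In Study design, Randomization and RCT design elements, and Delivery of intervention, replace the claim that clinical staff are blinded. State that bedside staff may become aware of the arm, and that masking of parents is intended but not ensured.
2. Instruct bedside staff not to tell families whether a device plays sound.
3. Ask parents to guess the arm (treatment, control, don't know) at device removal and again when the 18-month CDI is completed. The second question is needed because the arm could become known after discharge. Report the guesses by arm descriptively; with 21 per arm, any summary index would be imprecise.
4. Keep the intention-to-treat comparison of all families as the analysis that supports the conclusion. Treat any analysis by parental awareness as exploratory. Leaving out families who learned the arm is a post-randomization exclusion, likely to differ by arm, in a trial of 42 infants. If the guesses show leakage, describe the result as parent-reported with partial masking.

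**Cost.** Changed wording, a short staff instruction and one question asked twice; no extra infants or visits. The question may prompt some parents to speculate, and the blinding claim becomes less favourable.

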**Fig. 1 Fig1:**
[figure not shown]
Flow chart of the trial protocol. CDI, MacArthur-Bates Communicative Development Inventories; GA, gestational age; LENA, language environment analysis; MRI, magnetic resonance imaging; NICU, neonatal intensive care unit; PICN, Packard intermediate care nursery; PMA, postmenstrual age

### Participants

Preterm neonates born and admitted to the LPCH’s NICU at Stanford University will be eligible to participate. To be eligible, neonates must be born between 24-0/7 and 31-6/7 weeks GA (*N* = 42; T: *n* = 21 and C: *n* = 21). All races and ethnicities will be included. However, we will enroll infants whose family’s primary language is English or Spanish, because of our limitations in communicating with families using other languages. The primary language outcome, the CDI: Words and Gestures Questionnaire, will be administered in English or Spanish, as appropriate [37, 38]. Eligible participants must be free of the following adverse outcomes that could potentially confound language and neuroimaging outcomes: (1) congenital anomalies or recognizable malformation syndromes; (2) serious neurological conditions, including active seizure disorders, history of central nervous system infections or hydrocephalus, intraventricular hemorrhage grades III–IV, and cystic periventricular leukomalacia; (3) surgical treatment for necrotizing enterocolitis; (4) small for GA (< 3 percentile) and/or intra-uterine growth restriction; and (5) major sensori-neural hearing loss.

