### Outcome assessment methods

The primary outcome is language development (domain) assessed through the MacArthur-Bates CDI (measure) at (metric) 18 months AA (time point), quantified as expressive and receptive language raw scores and aggregated as group means (aggregation). The secondary outcome is white matter development (domain) assessed through dMRI scans (measure) collected at (metric) two different time points (time point): (1) prior to hospital discharge (neonatal time point) and (2) at 12 months AA (1-year time point), quantified with the dMRI metric (MD) and aggregated as group means (aggregation).

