#### Control variables and covariates

To characterize the sample and ensure balance across groups in analyses for treatment effects, we will prospectively collect the following information from electronic medical records and parent report questionnaires to control for (1) major medical complications associated with prematurity, including GA, birth weight, sex, history of antenatal steroid usage, infection, number of days of intubation and oxygen, and X-ray changes consistent with chronic lung disease; (2) PMA at MRI scan; (3) the number of nights of exposure to study treatment; and (4) sociodemographic factors associated with later language outcomes, including the SES of primary caretakers as measured by the HI [43], the frequency and number of languages spoken by adult and child household members, and number of siblings.

We will also obtain metrics to ensure balance across groups on the basis of the amount of language exposure experienced by infants in their home environments. To collect data on naturalistic maternal/caregiver input during the infancy period, we plan to use the Language ENvironment Analysis (LENA) recording device and software [54]. Families will be asked to perform two full-day (16 h) home LENA voice-recording sessions immediately around the time of the 12 months AA visit for MRI scanning. From this device, we will examine the adult words count measure per hour, normalizing for the length of audio recording, since it is the most accurate measure from LENA at this age when the infants may have limited language production skills [55]. If the groups do not match, we will use this language exposure metric as a covariate in the analyses.

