#### Analytic strategy

We anticipate that stratification prior to randomization will result in a close matching of T and C groups on demographic and health variables. Prior to statistical analyses, we will use independent samples t-tests (continuous variables) or chi-square tests (categorical variables) to assess the statistical balance between T and C groups on the basis of GA, sex, SES, clinical complications associated with premature birth, and language exposure during treatment and after hospital discharge. Analyses will use an intention-to-treat strategy [57]. If groups are matched on all variables, we will use independent t-tests (two-tailed) to compare T versus C groups on the primary long-term language outcome and the secondary short-term outcomes that relate to white matter development. Should groups not be balanced, and to account for missing data, we will use linear mixed models: T group as a fixed factor and unmatched or missing variables are random factors. Statistical significance is set at *p* < 0.05. Should an imbalance of twins or multiples occurs, we will perform group analyses including all singletons and one randomly selected twin or multiple from each set [58].

We will perform post hoc univariate and/or non-parametric analyses to determine if neural and clinical outcomes are associated with variations in the dose (i.e., number of hours of maternal speech delivered) or length (i.e., number of nights of delivery) of treatment, controlling for GA and PMA. Post hoc covariance analyses will permit further interpretation of either significant or non-significant treatment effects for short- and long-term neural and language outcomes. We will use multiple regression analyses to predict language outcomes from short-term neural and clinical outcomes, while controlling for group status and measures of language exposure.

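### The primary CDI analysis pools raw scores from English and Spanish forms in an unadjusted test; form language should be a prespecified fixed covariate, for precision

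*Protocol article*

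**What the plan says.** All references are to the protocol article.

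- **Participants.** The trial limits entry by language: "we will enroll infants whose family’s primary language is English or Spanish". The primary questionnaire "will be administered in English or Spanish, as appropriate", with two sources cited.
- **Outcome assessment methods.** The primary outcome at 18 months adjusted age is "quantified as expressive and receptive language raw scores and aggregated as group means". No section mentions norms, percentiles or scoring within form.
- **Randomization and RCT design elements.** Minimisation uses two factors: gestational age in two bands and socioeconomic status in two levels. Language is not one of them.
- **Analytic strategy.** Balance between arms is assessed "on the basis of GA, sex, SES, clinical complications associated with premature birth, and language exposure during treatment and after hospital discharge". If the arms match on everything, the primary comparison is a two-tailed independent t-test. If they do not, or if data are missing, a linear mixed model is used, with unmatched or missing variables entered as random factors.
- **Control variables and covariates.** The nearest planned variable is "the frequency and number of languages spoken by adult and child household members". The LENA adult word count measures how much speech is heard, not the language of the form.
- **Study design.** Parents complete questionnaires on demographics and language before randomisation.

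**The concern.** Expressive and receptive scores come from one of two language versions of a parent checklist, and the article neither claims nor supports a common raw scale for them. Averaging the raw scores assumes one. If one form tends to give higher scores than the other, that difference adds to the outcome's spread and, with 21 infants per arm, to chance differences between the arms.

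The stated method does nothing direct about this. Form language is not balanced at allocation, not named in the balance check and not in the t-test. The conditional route to the mixed model does not close the gap, for three reasons:

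- The number and frequency of household languages do not record which form was scored.
- The route opens only on imbalance or missing data, so it would not remove form-related noise when the arms look alike.
- It would enter the variable as a random factor, which suits a two-level variable poorly.

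At stake is the precision of the primary comparison in a small trial whose power at its smaller effect size has little margin.

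**Working it through.** **Inputs from the article:** 21 infants per arm, two-sided 0.05, Cohen's d = 1.0 with 0.9 as the smaller alternative (Participants; Power calculations; Analytic strategy).

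**Assumed inputs, because the article gives neither:** Spanish-form share p = 0.2 to 0.4; shift between forms g = 0.3 to 0.8, in within-form SDs. The design effect sizes are also read as multiples of the within-form SD.

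**Step 1. Reproduce the stated power (two-sample t-test, noncentral t).**

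- d = 1.0, power 0.8: n = 16.7, so 17 per arm (stated: 17).
- d = 1.0, n = 21: power 0.885 (stated: 0.88).
- d = 0.9, n = 21: power 0.812 (stated: greater than 0.8).

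All three reproduce. The stated figures are not wrong, but the last is only 0.012 above 0.8.

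**Step 2. Added variance from pooling.** The outcome variance is multiplied by 1 + p(1−p)g².

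- Smallest case: 0.2 × 0.8 × 0.3² = 0.0144, about 1%.
- Largest case: 0.4 × 0.6 × 0.8² = 0.1536, about 15%.

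**Step 3. The same effect seen as chance imbalance.** The SD of the difference between arms in Spanish share is √(2p(1−p)/21). Multiplying by g gives the SD of the resulting movement in the treatment contrast.

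- Smallest: √(2 × 0.2 × 0.8/21) × 0.3 = 0.123 × 0.3 = 0.04 SD.
- Largest: √(2 × 0.4 × 0.6/21) × 0.8 = 0.151 × 0.8 = 0.12 SD.

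The variance of the contrast itself is 2/21 (standard error 0.31 SD). Squaring the imbalance SD and dividing by 2/21 gives p(1−p)g², which is Step 2 again. The two figures describe one effect and must not be added together.

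**Step 4. Power with unadjusted pooling.** Replace d by d/√(1 + p(1−p)g²), with n = 21 per arm.

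| Shift g | Spanish share p | Power, d = 1.0 | Power, d = 0.9 |
|---|---|---|---|
| 0 | any | 0.885 | 0.812 |
| 0.3 | 0.2 | 0.881 | 0.807 |
| 0.3 | 0.4 | 0.879 | 0.804 |
| 0.5 | 0.2 | 0.873 | 0.797 |
| 0.5 | 0.4 | 0.867 | 0.789 |
| 0.8 | 0.2 | 0.853 | 0.773 |
| 0.8 | 0.4 | 0.837 | 0.755 |

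At d = 1.0 power stays above 0.8 throughout. At d = 0.9 it is below 0.8 at a shift of 0.5 SD for both shares.

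**Limits of the calculation.** It treats infants as independently allocated and ignores minimisation on gestational age and socioeconomic status. Twins and multiples go to the same arm and would normally share a family language, so chance imbalance is probably somewhat understated. Conversely, any association between language and socioeconomic status would let minimisation reduce it.

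**The case against.** The strongest case against is that the harm rests on an unseen difference between forms. Nothing in the article says that the two versions differ in length, level or scale, and citing two sources does not show it. A range starting at 0.3 SD presupposes a shift. This stands: with no shift there is no loss, and the sizes above are conditional. Even within the range, power at the design effect of d = 1.0 never falls below 0.8. It can also be said that covariate detail belongs in an analysis plan that is not shown. That carries less weight here, because the article itself fixes the metric, the aggregation, the balance list and the test.

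Three stronger readings are tempting, and the documents do not support them.

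- **That pooling biases the comparison.** A baseline trait unevenly split by chance is not systematic bias. Randomisation leaves the contrast unbiased in expectation, and the t-test's standard error already includes the extra spread, so type I error is not inflated on this account.
- **That the form is chosen after randomisation.** The article says only that the language will be the appropriate one. Family language is an entry condition, the language questionnaires come before randomisation, and the mother's storybook recording, in English or Spanish, is made before it too. These point to a trait known in advance.
- **That language could never enter the analysis.** The household-language variables are collected for control, and an unmatched variable moves the analysis to the mixed model. A related variable could therefore enter, though conditionally and as a random factor.

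**Conclusion.** The point holds as one of precision. The stated primary analysis treats raw scores from two language forms as one scale and has no direct provision for form language at allocation, in the balance check or in the test. If 20-40% of forms are Spanish and the forms differ by 0.3-0.8 SD, variance rises by 1-15% and the d = 1.0 power claim survives with less margin. The claim of power above 0.8 at d = 0.9 fails at shifts of about 0.5 SD or more. Both ranges are assumptions, as is reading d in within-form SDs. The expected loss is modest. The case for acting is that the remedy costs almost nothing and uses information collected before randomisation.

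**What to change.** In Analytic strategy, define form language (English or Spanish) for each infant from the family language questionnaire completed before randomisation. Enter it as a prespecified fixed covariate in the primary CDI model, for both the expressive and the receptive score, whether or not the arms look balanced. Keep the unadjusted pooled raw-score contrast as a sensitivity analysis.

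Standardising scores within form is not clearly better. At the assumed shares only about 8 to 17 of the 42 forms would be Spanish (0.2 × 42 = 8.4; 0.4 × 42 = 16.8), too few for a stable sample mean and SD, and the documents supply no published norms.

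The cost is one degree of freedom (39 rather than 40 for error with 42 infants) and a change of wording. No new data, visits or participants are needed. If a form effect exists, adjustment roughly restores the planned power of 0.885 at d = 1.0 and 0.812 at d = 0.9, less that degree of freedom.
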